##### Childhood Trauma Questionnaire (CTQ) [73]

The CTQ is a 28-item self-report retrospective inventory to measure childhood or adolescent emotional, physical, and sexual abuse, and emotional and physical neglect. A 5-point scale is used, ranging from 1 (never true) to 5 (very often true). The psychometric properties of the German version are similar to the American original [74].

##### Dissociation Tension Scale (DSS) [75]

The DSS is a self-rating instrument for the assessment of psychological and somatoform dissociative features (ranging from normal up to pathological) as well as of aversive inner tension, occurring within the past 7 days. The DSS contains 21 items, rated on a time-oriented scale ranging from 0% (never) to 100% (constantly).

#### Primary outcome measure

##### Distress dimension of the Psychotic Symptom Rating Scales—Auditory Hallucination subscale (PSYRATS-AH) [30]

The PSYRATS-AH is a structured interview examining 11 dimensions of auditory hallucinations (i.e., frequency, duration, location, loudness, beliefs regarding the origin, amount of negative content, degree of negative content, amount of distress, intensity of distress, disruption, control), each rated on a 5-point scale, with higher scores representing greater overall severity of voice hearing experiences. Items are grouped in four subscales measuring distress (negative content, distress, and control), frequency (frequency, duration, disruption), attribution (location and origin of voices), and loudness (loudness item only) [76]. The German version achieved good reliability and validity scores [77].

#### Secondary outcome measures

##### Revised Beliefs About Voices Questionnaire (BAVQ-R) [78]

The persecutory beliefs subscale [79] of the BAVQ-R will be used in the current study to assess perceived hostile intent and power of voices. The BAVQ-R is a self-report measure of cognitive, emotional, and behavioral responses to voices. It consists of 35 items rated on a 4-point Likert scale from 0 (disagree) to 3 (strongly agree). The original measure included five subscales, three relating to beliefs about voices (i.e., malevolence, benevolence, and omnipotence) and two relating to emotional and behavioral responses to voices (i.e., engagement and resistance). For the German version, the beliefs subscales with the exception of the omnipotence subscale showed satisfying internal consistency and good test-retest-reliability [38]. A recent study examining the factor structure of the BAVQ-R supported a two-factor (persecutory beliefs combining omnipotence and malevolence, and benevolent beliefs) instead of the proposed three-factor beliefs model [79].

##### Voice and You-Revised (VAY-R) [39]

The voice dominance and intrusiveness subscales of the VAY-R will be used to assess dysfunctional beliefs about voices. The VAY-R is a brief version of the VAY [80] measuring both the extent of a perceived aggressive relating of the voice in terms of dominance and intrusiveness and the extent of reciprocal submissive (i.e., hearer dependence) and avoidant (i.e., hearer distance) relating preferences of the voice-hearer. It consists of 14 items, measured on a 4-point scale ranging from 0 (seldom) to 3 (nearly always). The VAY has good internal consistency and acceptable test-retest reliability [80]. The psychometric properties of the German version are currently under examination by Lincoln et al. [37].

##### Approve questionnaires [40]

The Approve-Voices and the Approve-Social measures each consist of 15 items measuring functional assertive and dysfunctional non-assertive (i.e., passive or aggressive) relating to voices and to other people, respectively. Items are scored on a 10-point Likert scale, ranging from 0 (disagree completely) to 10 (agree completely). The Approve questionnaires have been found to be reliable and valid in both their English [40] and German versions, with the German validation study being currently in preparation for publication [37].

##### Brief Core Schema Scales (BCSS) [41]

The BCSS is a self-report measure of schemata concerning self and others in psychosis with good psychometric properties. The 24 items are rated on a 5-point Likert scale from 0 (I do not hold the belief) to 4 (I believe it totally) and form four subscales, assessing negative self, positive self, negative other, and positive other.

#### Other outcome measures

##### Depression, Anxiety and Stress Scale-21 (DASS-21) [81]

The 21-item version of the DASS-21 will be administered to assess for features of depression (depression subscale), hyperarousal (anxiety subscale), and tension (stress subscale) over the previous week. The items are rated on a 4-point Likert scale from 0 (did not apply to me at all) to 3 (applied to me very much, or most of the time). Psychometric properties have been established in clinical and community samples [82–84] for the original version as well as for the German version [43].

##### Clinical Global Impression Scale—Severity (CGIs) [44]

The CGIs is an observer-rated global measure of symptom severity within the past 7 days that has been widely used in clinical trials. It ranges from 1 (not ill at all) to 7 (severely ill).

##### Social and Occupational Functioning Assessment Scale (SOFAS) [45]

The SOFAS is an observer-rated measure of the individual’s level of social and educational/occupational functioning, independently of the severity of the individual’s psychopathology. The scale ranges from 0 to 100, with higher scores indicating better functioning.

##### Quality of Life Enjoyment and Satisfaction Questionnaire (Q-LES-Q-18) [46]

The Q-LES-Q18 is a self-report questionnaire assessing life satisfaction in five dimensions: physical health, subjective feelings, leisure activities, social relationships, and medication. Its 18 items are rated on a 5-point scale, with (1) denoting “not at all” and (5) “all the time.”

##### Treatment satisfaction questionnaire

A short questionnaire was developed for the current study to assess satisfaction with the study procedure and the CBTv-based EMI under examination. The items are rated on a 7-point Likert ranging from 1 (not true at all) to 7 (completely true).

Researchers will receive training in the administration of the clinical interviews before they start conducting the assessments. Additionally, the maintenance of high-quality diagnostic assessments will be facilitated by continuous supervision.

#### EMA

The two EMA periods will last 9 days each and have a time-contingent design with a semi-random sampling schedule. Participants will receive ten text messages a day between 8:00am and 10:30pm, prompting them to complete an EMA survey. Each prompt will take place randomly within equal intervals of 60 min, with 30 min between intervals in order to prevent prompts occurring too close together. Each EMA survey takes approximately 2–3 min to complete and assesses sleeping problems (only in the first survey of the day); affective state; self-esteem; the occurrence of voices since the previous assessment; perceived distress of voices; beliefs about voices; passive, aggressive, and assertive relating to voices; social contact since the last assessment; passive, aggressive, and assertive relating to other people; and dissociative experiences, traumatic memories, non-suicidal self-injury, suicidal thoughts, and alcohol and drug consumption since the last assessment. A full list of the EMA items is provided in Additional file 1.

Before the baseline EMA, participants will be instructed how to use the EMA and practice its usage by going through a survey to ensure that each item is understood and appropriately rated. They will be given a written confirmation of participation in the study, which can be presented to teachers at school or supervisors at work if required. Participants will be encouraged to contact the research team immediately if they have any questions or technical issues related to the EMA.

### Plans to promote participant retention and complete follow-up {18b}

Efforts will be made to engage participants in as many assessments as possible and achieve a high adherence rate in the EMA. Appointments for the assessments will be offered at times and locations, which best suit the participants. Additionally, during assessments, breaks will be offered and the assessments can be split into serval shorter sessions if required. Participants adherence to the assessment schedules of the two EMA periods and the EMI will be monitored electronically by the research team, using the administration tool of the web-based software program ASMO. Participants showing a significant drop in their response rate will be contacted by the research team to clarify the reasons of non-adherence, boost motivation, and offer problem-solving and support when needed. Participants will be reimbursed for participation in the baseline assessment (T0) with 75 CHF, and for the participation in the 3-month (T1) and 6-month (T2) follow-up assessments with 25 CHF each. Additionally, they will get reimbursed for each completed survey of the two EMA periods with 0.50 CHF (90 CHF in total) and with additionally 10 CHF for a completion rate of ≥ 70%. Retention rates will be continuously monitored by the principal investigator throughout the trial.

### Data management {19}

Diagnostic interview and self-report data assessed at baseline (T0), 3-month follow-up (T1), and 6-month follow-up (T2) will be collected in encrypted form and managed using REDCap (Research Electronic Data Capture) tools hosted at the University Bern, Switzerland [51, 52]. REDCap is a secure, web-based software platform designed to support data capture for research studies, providing (1) an intuitive interface for validated data capture; (2) audit trails for tracking data manipulation and export procedures; and (3) automated export procedures for seamless data downloads to common statistical packages. The exported data will be stored on the end-to-end encrypted cloud storage system (Tresorit: www.tresorit.com) of the research department of the University Hospital of Child and Adolescent Psychiatry and Psychotherapy Bern, University of Bern, Switzerland. The storage system is regularly backed up and checked by the biostatistician (SL) of the trial.

The EMA/I data collected via the web-based software program ASMO will be stored in encrypted form on secure servers, located at the Centre for Psychotherapy Research, University of Heidelberg, Germany. A distributed Replicated Block Devide (DRBD)-based cluster will provide synchronous replication of all data during data entry on two separate servers. In addition, incremental backups will be conducted following a predefined schedule. The EMA/I will be transferred via an encrypted, password-protected data exchange portal located at the server of the Centre for Psychotherapy Research, to the end-to-end encrypted cloud storage system Tresorit of the research department of the University Hospital for Child and Adolescent Psychiatry and Psychotherapy, University of Bern, Switzerland. Afterwards, the EMA/I data stored in Heidelberg will be deleted.

All members of the research team involved in the collection and management of data will be given training on how to use the web-based software programs REDCap and ASMO. The researchers involved in the day-to-day data collection will be supervised by the principal investigator (MC) and the biostatistician (SL) of the trial. Data collection and management will be a standing item on the agenda of the weekly meeting of the research team.

### Confidentiality {27}

All data collected within the trial will be kept confidential and be handled with uttermost discretion. Confidentiality will only be broken if participants disclose any information that indicates a risk for themselves or others. Data collection via REDCap and ASMO will occur in encrypted form only. The coding key linking a unique participant number with personal data of participants will be stored in a password-protected file on the end-to-end encrypted cloud storage system Tresorit of the research department of the University Hospital for Child and Adolescent Psychiatry and Psychotherapy, University of Bern, Switzerland. Physical data, such as consent forms, will be locked in filing cabinets of the research department of the University Hospital for Child and Adolescent Psychiatry and Psychotherapy, University of Bern, Switzerland. The coding key, the consent forms, and all used electronic systems (i.e., REDCap, ASMO, Tresorit) will be only accessible to authorized personnel who fulfill their duties within the scope of the trial. Further, the electronic systems have built-in audit trails that log all user activity. The data storage will be continuously monitored by the principal investigator (MC) and the biostatistician (SL) of the trial. Data will be analyzed and published in aggregated and encrypted form only.

### Plans for collection, laboratory evaluation, and storage of biological specimens for genetic or molecular analysis in this trial/future use {33}

Not applicable—this trial does not involve collecting biological specimens.

## Statistical methods

### Statistical methods for primary and secondary outcomes {20a}

Descriptive statistics within each randomized group will be presented for all variables assessed at baseline (T0), 3-month follow-up (T1), and 6-month follow-up (T2). To examine the effect of CBTv-based EMI on the primary outcome of voice distress (PSYRATS-AH Distress), multilevel regression models will be applied, with the participants’ ID as random, as well as group allocation (TAU + CBTv-based EMI versus TAU), time (T0, T1, T2), and PSYRATS-AH Distress at baseline as fixed effects. Multilevel modeling is advantageous over traditional methods of repeated-measures analysis, as it uses all available data and is unaffected by randomly missing data (135). The same approach will be used to analyze the effects of the CBTv-based EMI on secondary and other pre-specified outcomes. All analyses will be run based on the intention-to-treat principal (ITT) and be adjusted for confounding variables (e.g., sex, age). Standardized effect sizes will be reported. If needed, significance level adjustment will be applied to prevent accumulation of the type I error. Statistical analyses will be carried out using Stata Statistical Software [53] or R [85].

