### Outcomes {12}

The primary outcome of the study is the change in the Distress dimension of the Psychotic Symptom Rating Scales Auditory Hallucinations subscale (PSYRATS-AH) [30] between the baseline (T0) and the 3-month follow-up (T1) assessments. Reducing the level of psychological distress due to voice-hearing (instead of reducing hearing voices per se) is the main therapy aim of CBTv and the PSYRATS-AH has been widely used in clinical trials investigating the efficacy of CBTv in the past [17, 35, 36]. Additionally, distress is the prioritized outcome by patients with voices and is related to dysfunction [37].

Secondary outcomes of the study include the change in (1) voice-related distress (distress dimension of the PSYHRATS-AH) between T0 or T1 and the 6-month follow-up (T2); (2) perceived hostile intent and power of voices (Persecutory Beliefs subscale of the Revised Beliefs About Voices Questionnaire; BAVQ-R) [38]; and (3) perceived voice dominance and intrusiveness (Voice and You-Revised; VAY-R) [39], passive, aggressive, and assertive relating to voices (Approve questionnaires) [40], and negative core beliefs about the self (Brief Core Schema Scales, BCSS) [41] between T0, T1, and T2. Appraisals of and relating styles to voices as well as core beliefs about the self were chosen as secondary outcomes because they represent potential mediators of the efficacy of the CBTv-based EMI [35, 42].

Other outcomes include changes in (1) severity of depression, anxiety, and stress (Depression, Anxiety and Stress Scale-21 (DASS-21) [43]); (2) overall illness severity (Clinical Global Impression Scale-Severity (CGIs) [44]); (3) psychosocial functioning (Social and Occupational Functioning Assessment Scale (SOFAS) [45]); and (4) quality of life (Quality of Life Enjoyment and Satisfaction Questionnaire (Q-LES-Q-18) [46]) between T0, T1, and T2.

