### Sample size {14}

Sample size calculation was based on the expected difference between the TAU + CBTv-based EMI group and the TAU group in the severity of the PSYRATS-AH Distress dimension between the baseline (T0) and the 3-month follow-up (T1) assessments. Pilot studies examining the efficacy of the CBTv that is adopted for use as EMI in the current trial reported large effect sizes (Cohen’s *d* ranging between 1.3 and 1.78) [35, 42]. Given that these studies involved face-to-face therapy and that effect sizes are likely to be reduced in a full-scale trial, a medium effect size is targeted in the current study. A power-analysis for an analysis of variance with two groups (TAU + CBTv-based EMI, TAU), and two repeated measures (T0, T1) and within-between interaction (group x time), was calculated using G*Power 3.1.9.4 [48]. Assuming a medium effect size of *f* = 0.25, a power of 0.80, and an alpha level of .05, a sample size of *N* = 128 is required. Including an expected attrition rate of 20%, the required total sample size for the RCT is *N* = 154, with 77 participants in each treatment arm.

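### Baseline distress is both an outcome row (T0) and a covariate in the primary model, which is defective with or without a group by time term

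*Protocol article*

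**What the plan says.** All references are to the protocol article.

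- **Statistical methods {20a}** specifies a multilevel regression with the participant's "ID as random, as well as group allocation" and then "time (T0, T1, T2), and PSYRATS-AH Distress at baseline as fixed effects". T0 is thus a level of time, and the T0 score is also a covariate. No group by time term is listed, and nothing says that the T0 row is removed. The same approach is extended to the secondary and other outcomes, and section {20b} repeats the model for the moderator analyses.
- **Outcomes {12}** defines the target: "The primary outcome of the study is the change in the Distress dimension" of the PSYRATS-AH between T0 and T1.
- **Sample size {14}** powers a different term from any listed in {20a}: a two-group analysis of variance with "two repeated measures (T0, T1) and within-between interaction (group x time". It expects 20% attrition and sets 77 participants per arm.
- **Section {20c}** relies on the multilevel model, without imputation, to deal with dropout and requires every randomised participant to be analysed.

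**The concern.** Baseline can be handled as a covariate for later measurements or as the first of the repeated outcomes. Doing both makes the T0 score predict itself. One slope is fitted to T0 rows, where the true slope is 1, and to T1 and T2 rows, where it is about the pre-post correlation. The covariate is also constant within a person, so it can do little for a contrast built from within-person change.

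At stake are the size of the reported primary effect if no group by time term is fitted. If one is fitted, the precision expected from baseline adjustment and the validity of the standard error under dropout are at stake instead.

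**Working it through.** **Inputs.** From the protocol: 77 per arm, 20% attrition, T0/T1/T2 as occasions, "Assuming a medium effect size of *f* = 0.25" and "a power of 0.80, and an alpha level of .05". Assumed, because the protocol gives none of them: pre-post correlation r of 0.3, 0.5 or 0.7, plus one unequal set (T0-T1 0.5, T0-T2 0.35, T1-T2 0.7); dropout before T1, either completely at random or dependent on baseline; SD 1 at each occasion; the same effect at T1 and T2; independent, equal-variance residuals around the random intercept.

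**1. The plan's own figure.** With noncentrality f² × N = 0.0625 × 128 = 8, power is 0.801, so N = 128 is reproduced. This equals a two-sample t-test with d = 0.5 and 64 per arm, that is, an unadjusted comparison.

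**2. Literal model (no group by time term).** The group coefficient averages the effects at the three occasions.
- Complete data: (0 + 0.50 + 0.50)/3 = 0.33. Simulation: 0.33.
- 20% dropout, weighting by rows: (0.8 × 0.50 + 0.8 × 0.50)/(1 + 0.8 + 0.8) = 0.80/2.6 = 0.31. Simulation: 0.30 to 0.31.
- Simulated type I error: 5.1 to 5.9%.

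**3. Model with group by time, complete data.** The covariate adds the same amount to a person's T0 and T1 fitted values, so it vanishes from the T1 minus T0 contrast. In 3,000 simulated trials per scenario the estimate with and without the covariate differed by at most 0.0000.
- Variance of the change difference: 2 × 2(1 − r)/77. At r = 0.5 this is 2/77, SE 0.161.
- Variance of ANCOVA at T1: 2(1 − r²)/77. At r = 0.5 this is 1.5/77, SE 0.140.
- Ratio: 2(1 − r)/(1 − r²) = 2/(1 + r), which is 1.33 at r = 0.5 and 1.18 at r = 0.7.

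**4. Model with group by time, 20% dropout.** Cancellation is no longer exact. At r = 0.5 the common slope is close to the row-weighted mean (1 + 0.8 × 0.5 + 0.8 × 0.5)/2.6 = 0.69. A T0 residual is then only 0.31 of the centred baseline score, variance about 0.10, against 1 + 0.69² − 2 × 0.69 × 0.5 = 0.79 at T1. Dropouts contribute only the small T0 residuals, which pull down the pooled residual variance.

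Simulated results under no effect (3,000 trials each; simulation error of a 5% rate is about 0.4 points):

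| r | Dropout | Model SE / true SE, T0 used twice | Type I error, T0 used twice | Type I error, T0 covariate only | Type I error, T0 outcome only |
|---|---|---|---|---|---|
| 0.3 | baseline-dependent | 0.928 | 7.1% | 5.4% | 5.4% |
| 0.5 | random | 0.936 | 6.7% | 5.4% | 5.2% |
| 0.5 | baseline-dependent | 0.924 | 7.2% | 5.4% | 5.2% |
| 0.7 | random | 0.934 | 7.0% | 5.4% | 5.6% |
| 0.7 | baseline-dependent | 0.919 | 7.2% | 5.5% | 5.3% |
| unequal | random | 0.930 | 7.0% | 4.7% | 5.5% |
| unequal | baseline-dependent | 0.915 | 7.4% | 4.5% | 5.9% |

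A repeat simulation at r = 0.5 gave an SE 4 to 7% too small and a type I error of about 6 to 7%. Removing either use of T0 brings the error back close to 5%, which identifies the double use as the main cause.

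**5. Power at 0.5 SD, 20% dropout.** With T0 used twice: 84% at r = 0.5 and 96% at r = 0.7. With T0 as covariate only: 89% and 97 to 98%. At r = 0.3 the figures are 71% and 82 to 83%; with T0 as outcome only, power there is 68 to 69%.

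**The case against.** The strongest reply is that {20a} lists no group by time term, so neither the cancellation nor the inflated error belongs to the model as written. That stands. A reader might infer that the stated test rejects too often, but on the literal text its type I error is near nominal. The literal model has another fault: its coefficient is diluted by the T0 row. Since {12} and {14} both target T0 to T1 change, the interaction reading is reasonable, though still an inference.

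It can also be said that an unadjusted change comparison is unbiased under randomisation and is what the trial was powered for. That is correct: the precision loss is relative to ANCOVA, not to the sample size plan. A reader might infer that the trial is underpowered. At r = 0.5 or more the documents do not support this, since power stays above the stated 80%. Part of the 84% at r = 0.5 comes from the small standard error; using the true SE of 0.178, 0.5/0.178 − 1.96 = 0.85, which is a power of about 80%. The 71% at r = 0.3 reflects mainly the low correlation, which makes 0.5 SD a smaller fraction of the SD of change.

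A reader might add chance baseline imbalance as a further bias. It is the same loss seen another way: 2(1 − r) = (1 − r²) + (1 − r)², and the last term is the carried-over imbalance, already inside the standard error.

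Finally, the article does not state the residual covariance, and a fuller document may do so. The dropout result therefore depends on the usual random-intercept default. The double listing of T0 is stated text, however, not an omitted detail.

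**Conclusion.** The point holds, with consequences that depend on the reading. Without a group by time term, a 0.50 SD effect is reported as about 0.33 with complete data or 0.30 to 0.31 with 20% dropout, and the coefficient is not the one {12} asks for. With the term, the named adjustment gains no precision in complete data. Under 20% dropout the standard error is roughly 4 to 9% too small, and the type I error is about 6 to 7% instead of 5%.

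The inflation is moderate, is absent with complete data, and rests on assumed correlations, an assumed dropout mechanism and independent residuals; its direction was the same in every scenario tried. Exact cancellation needs complete data. No reading of the listed model gives the baseline-adjusted T1 effect that the text appears to intend.

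**What to change.** Use baseline once, and state the group by visit contrast at T1 as the primary test. Either of these will do:

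1. Model T1 and T2 only, with baseline distress, baseline by visit and group by visit as fixed effects.
2. Keep T0, T1 and T2 as outcomes, drop the baseline covariate, constrain the two arms to a common T0 mean, and use an unstructured covariance.

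The second keeps every randomised participant in the model, including those with no follow-up, and so fits {20c} better. Carry the same change to the secondary and other outcomes and to the moderator models in {20b}. The cost is a wording change, to be made before outcomes are analysed by arm; both models are standard in Stata and R, the packages already named.

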### Trial design {8}

This is a prospective, multicenter, assessor-blinded, two-armed, parallel-group, superiority RCT, using a 1:1 allocation. After providing written informed consent, participants will undergo a baseline assessment (T0) followed by a 9-day EMA. Afterwards, participants will be randomized to the intervention group or the control group. For the next 8 weeks, the intervention group will receive a CBTv-based EMI in addition to TAU, while the control group will receive TAU only. Afterwards, both groups will undergo another 9-day EMA, followed by a 3-month follow-up assessment (T1), and a 6-month follow-up assessment (T2). Figure 1 displays the Consolidated Standards of Reporting Trials (CONSORT) flow diagram of the study procedure.

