## Assignment of interventions: allocation

### Sequence generation {16a}

Randomization will be performed by the biostatistician of the University Hospital for Child and Adolescent Psychiatry and Psychotherapy, University of Bern, Switzerland (SL). Minimization, a covariate adaptive randomization, will be applied, which sequentially assigns each new participant to one of the two treatment arms by taking into account previous assignments of participants and specific covariates. This method ensures balance in important prognostic factors without the pitfalls of stratified randomization [49]. Imbalance is calculated according to Pocock and Simon [50]. In this trial, minimization will balance whether (a) voices are experienced daily or not (PSYRATS-AH item 1 (frequency) score 1 versus ≥2) and (b) participants receive any psychiatric/psychological treatment or not, because these variables are predicted to have an effect on treatment response and should therefore be balanced across groups.

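### The two minimisation factors, chosen because they are expected to predict response, are not named in the analysis model; leaving them out could make the test somewhat conservative

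*Protocol article*

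**What the plan says.** Protocol article, Sequence generation {16a}: "minimization will balance whether (a) voices are experienced daily or not (PSYRATS-AH item 1 (frequency) score 1 versus ≥2) and (b) participants receive any" psychiatric or psychological treatment. The reason given is "because these variables are predicted to have an effect on treatment response and should therefore be balanced across groups". The method is minimisation: "Imbalance is calculated according to Pocock and Simon". The probability of following the minimising arm is not stated. Trial design {8} describes a "superiority RCT, using a 1:1 allocation".

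Protocol article, Statistical methods for primary and secondary outcomes {20a}: a multilevel regression with a random participant effect, and with group, "time (T0, T1, T2), and PSYRATS-AH Distress at baseline as fixed effects". Secondary and other outcomes are handled in the same way. All analyses are to "be adjusted for confounding variables (e.g., sex, age" and so on, in an open list of examples.

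The section on additional analyses {20b} includes continuous versus non-continuous voices as an exploratory moderator, but does not say that this is the daily/non-daily factor used for allocation. Current treatment is not named in any analysis model.

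**The concern.** Minimisation removes most of the chance imbalance between arms on the factors it uses. If those factors are prognostic, the treatment difference then varies less from trial to trial than under simple randomisation. A model without the factors does not know this. It still counts their contribution as residual variance, so its standard error is larger than it should be. The usual remedy is to analyse by the factors used in allocation.

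Here the protocol calls two variables predictive of response and builds the allocation on them. When it turns to covariates, it names other ones. What is at stake is precision and power, not validity: intervals wider than necessary and a true type I error below the nominal 5%.

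**Working it through.** **The plan's own figure.** Sample size {14} states: "Assuming a medium effect size of *f* = 0.25, a power of 0.80, and an alpha level of .05, a sample size of" 128. For two groups, the noncentrality is λ = f²N = 0.0625 × 128 = 8. The noncentral F with 1 and 126 degrees of freedom gives power 0.801, so 128 reproduces, with f = 0.25 equivalent to d = 0.5. For attrition: "Including an expected attrition rate of 20%, the required total sample size for the RCT is" 154, which is 128 × 1.2 = 153.6. Neither figure is disputed here. They set the scale: about 154 × 0.8 = 123 analysed, for an effect of 0.5 SD.

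**Assumed inputs (not in the document).** Two binary factors, each with prevalence 0.6. Each shifts distress by s = 0.4, 0.6 or 0.8 SD. The correlation of T0 with T1 within factor levels is ρ = 0.5. The factor variance is v = 2 × 0.6 × 0.4 × s² = 0.48s², that is 0.0768, 0.1728 and 0.3072. Below, the excess is the model standard error without the factors divided by that with them, minus 1.

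**Case A: T1 ANCOVA, factors act only after baseline.** The residual variance given T0 is 1 − ρ² = 0.75 with the factors and 0.75 + v without them, so the ratio is √((0.75 + v)/0.75).

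**Case B: T1 ANCOVA, factors act equally at T0 and T1.** Baseline distress already carries part of the factor effect. The residual variance without the factors is (1 + v) − (0.5 + v)²/(1 + v), that is 0.768, 0.787 and 0.809, against 0.75 with them.

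| Shift per factor | Share of residual variance (A) | SE ratio, A | SE ratio, B |
|---|---|---|---|
| 0.4 SD | 0.0768/0.8268 = 9% | 1.05 | 1.01 |
| 0.6 SD | 0.1728/0.9228 = 19% | 1.11 | 1.02 |
| 0.8 SD | 0.3072/1.0572 = 29% | 1.19 | 1.04 |

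Simulated minimisation (124 analysed, probability 0.8 of following the minimising arm) agrees for case A, with ratios 1.051, 1.112 and 1.189. Without the factors, type I error there is 4.2%, 3.6% and 2.5%. Power for 0.5 SD is 87%, 85% and 80%, against 89% with them. In case B, power without them is 89%, 87% and 87%, against 89%.

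**Case C: within-person contrast.** In a random-intercept model with a group-by-time term and T0, T1 and T2 all as outcomes, a factor effect that is constant over time cancels from T1 − T0. In a simulation with 124 participants and shifts of 0.6 SD, the standard error of the T1 interaction was 0.1766 with or without the factors as main effects, differing by less than 0.00001. Here there is no excess, and main effects change nothing. If the factors predict change instead, main effects still do not capture it; factor-by-time terms would.

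**Scaled by variance explained.** A second simulation of a baseline-adjusted analysis used 128 analysed, probability 0.9 of following the minimising arm, and factors that together explain a set share of the variance left after baseline distress.

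| Variance explained | Type I error, factors omitted | Power, omitted | Power, included |
|---|---|---|---|
| 0% | 0.050 | 0.80 | 0.80 |
| 5% | 0.047 | 0.80 | 0.82 |
| 10% | 0.038 | 0.81 | 0.84 |
| 20% | 0.030 | 0.83 | 0.88 |
| 30% | 0.019 | 0.85 | 0.92 |

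With the factors included, type I error stays between 0.046 and 0.052.

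**The case against.** A reader might infer that the analysis will not adjust for the minimisation factors. The text does not support that. Sex and age are given only as examples, and an open list excludes neither factor. The two sections do not contradict each other; one simply does not name what the other relies on.

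A reader might also object that the open covariate list lets covariates be picked after the data are seen. This is a journal article, and neither the full protocol nor an analysis plan is shown. A complete covariate list is commonly left to those documents, so its absence here is not a fault. What remains is narrower: where the article does describe the model, it omits the variables that its own allocation depends on.

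The strongest objection concerns size. The 5% to 19% excess needs a T1-only ANCOVA with factors that act beyond baseline distress. The stated model has three time levels including T0, the sample size section powers a group-by-time interaction, and the outcomes section defines the primary outcome as change from T0 to T1. Read together, these point towards case C, where the excess vanishes and main effects alone would achieve nothing. Both factors are also baseline characteristics, so baseline distress may already carry much of their effect, as in case B. This objection stands, and it limits the claim. It does not remove it: the model as described names no interaction, so the contrast that carries the test is not settled, and the protocol itself expects these variables to affect response.

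**Conclusion.** The point holds as a possible loss of precision of unknown size. If the two factors are left out and predict follow-up distress beyond baseline, the standard error is too large and the test conservative. Under assumed shifts of 0.4 to 0.8 SD per factor, the excess is about 5% to 19% in the most favourable case for the point, about 1% to 4% if the factors act equally at T0 and T1, and nil for a pure within-person contrast. If the factors explain nothing, nothing is lost.

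A reader might infer bias in the treatment effect or a raised false-positive rate. Neither follows: the estimate is unbiased and any error in the type I rate is downwards. Nor is the trial shown to fall below its power target for this reason. Even the largest shift in case A leaves simulated power at 80%. The factor strengths, their prevalence, the T0-T1 correlation and the allocation probability are all assumptions.

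**What to change.** In the statistical methods section, name both minimisation factors (PSYRATS-AH item 1 score 1 versus 2 or more; any versus no psychiatric or psychological treatment at allocation) as fixed effects, together with baseline distress, in the primary model. Name both factors likewise in the models for secondary outcomes.

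Match the form to the contrast. If the treatment effect is a group-by-time contrast with T0 among the outcomes, add factor-by-time terms as well, since main effects alone would not help. Alternatively, analyse T1 and T2 as outcomes with T0 as a covariate.

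The cost is two degrees of freedom for the main effects. With three visits, factor-by-time terms take 2 factors × 2 = 4 more. No new data are needed: the Concealment mechanism section {16b} has the allocation covariates entered in REDCap before assignment. The change should be made before outcome data by arm are seen.
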